**Summary of Study Protocol**

| **Project Name** | A study protocol of the rehabilitative efficacy of cardiovascular ultrasound therapy after percutaneous coronary intervention in patients with coronary artery disease: A multicenter, parallel-group, randomized controlled study |
| --- | --- |
| **Objective** | The aim of this study is intended to evaluate the rehabilitative efficacy of cardiovascular ultrasound therapy in patients with coronary artery disease (CAD) who had already undergone percutaneous coronary intervention (PCI). Specifically, the study aims to examine the effects of cardiovascular ultrasound therapy on inflammatory markers, serum lipids, endothelial function, cardiac function, carotid artery plaque, and hemodynamics. In addition, the study will analyze patients’ heart rate variability (HRV), record their symptoms, and score depression and anxiety. |
| **Research Hypothesis** | Cardiovascular ultrasound therapy has the potential to reduce perioperative myocardial damage, reduce the production of inflammatory factors and inflammatory cells, and has a certain regulatory effect on blood lipids, platelet function, hemodynamics and blood pressure in patients after PCI. |
| **Study Design** | This study is a multicenter, parallel-group, randomized controlled clinical trial. Subjects were enrolled by randomization into groups of 20 per center, with 10 in the control group and 10 in the treatment group. Each participating unit completes the relevant content of the subject case list. |
| **Subject population** | **Inclusion Criteria:**  • Age at enrollment: 18 years or older;  • Confirmed CAD requiring elective PCI;  • Thrombolysis in myocardial infarction (TIMI) flow grade 2 or above after PCI;  • No intraoperative complications following PCI, such as entrapment, reflux, or perforation of the coronary artery;  • Intact skin in the anterior chest area;  • Cardiac enzymes and troponin I within normal range.  **Exclusion Criteria:**  • ST-segment elevation myocardial infarction and non–ST-segment elevation myocardial infarction;  • Occlusion of branch vessels during PCI;  • Perioperative use of hormones or immunosuppressants;  • Combined infection or other inflammatory diseases;  • Postoperative fever;  • Allergy to contrast media or cardiovascular ultrasound acoustic head–related materials;  • Changes in lipid-lowering, antiplatelet, and antihypertensive drug regimens during treatment;  • A clear diagnosis of autoimmune disease;  • A history of other surgeries or trauma in the preceding 7 days;  • Infection with the novel coronavirus during the preceding month;  • Previous PCI treatment;  • Previous cardiovascular ultrasound treatment;  • Diabetes mellitus. |
| **Diagnostic criteria** | The diagnosis of coronary heart disease refers to the diagnostic criteria of the American Heart Association, and the lumen diameter of at least one or more major coronary arteries is confirmed by coronary angiography to be narrowed by ≥50%, combined with medical history, electrocardiogram and coronary CTA. |
| **Sample size** | The sample size of the intervention group and the control group was calculated using PASS 15 software. Our calculations of sample size and power are based on the primary outcomes, utilizing a two-sided analysis with a statistical power of 90% (1 – β = 0.90) and a significance level of α = 0.05. Owing to the lack of prior studies examining cardiovascular ultrasound therapy following PCI, the sample size was determined following an extensive evaluation by a panel of experts. Targeting long-term inflammation and cardiovascular efficacy, they selected high-sensitivity C-reactive protein (hsCRP) as the primary biomarker, given its relevance and the larger sample size required by interleukin 6. Cardiovascular ultrasound is estimated to reduce hsCRP levels by an average of 4 mg/L. To meet this target, 160 participants (80 per group in a 1:1 allocation) are projected to be needed. Factoring in an anticipated dropout rate of 20%, the final sample size would be adjusted to 200 participants (100 per group), ensuring adequate statistical power and robustness for the study’s objectives. |
| **Study outcomes** | 1. **Primary** **outcome**   The primary outcome measures will focus on the levels of hsCRP and interleukin-6 in the peripheral serum.   1. **Secondary outcome**   **1.1 Indicators of serum myocardial injury and blood lipid levels**  Serum biomarkers indicative of myocardial injury encompass creatine kinase isoenzymes (CK-MB), cardiac troponin I (c-TnI), and myeloperoxidase (MPO). Lipid profile markers in serum comprise total cholesterol (TC), triglycerides (TG), low-density lipoprotein cholesterol (LDL-c), high-density lipoprotein cholesterol (HDL-c), apolipoprotein A (ApoA), apolipoprotein B (ApoB), lipoprotein (a), and oxidized low-density lipoprotein (ox-LDL) in the peripheral blood.  **1.2 Serum markers of endothelial function**  The serum markers utilized to assess endothelial function encompass endothelial nitric oxide synthase (eNOS), endothelin-1 (ET-1), and vascular endothelial growth factor (VEGF) in the peripheral blood.  **1.3 Serum markers of endothelial function**  The serum markers utilized to assess endothelial function encompass endothelial nitric oxide synthase (eNOS), endothelin-1 (ET-1), and vascular endothelial growth factor (VEGF) in the peripheral blood.  **1.4 Serum inflammatory factors**  Each morning, 5 mL of fasting venous blood will be drawn by nursing staff to assess the proportion of inflammatory cells and measure levels of inflammatory markers in the peripheral blood.  **1.5 Hemodynamic parameters**  These encompass a comprehensive range of indicators, including cardiac index (CI), cardiac output (CO), stroke volume (SV), stroke volume index (SVI), mean arterial pressure (MAP), stroke systemic vascular resistance index (SSVRI), left ventricular stroke work index (LVSWI), systemic vascular resistance index (SVRI), ejection phase contraction index (EPCI), inotropic state index (ISI), systemic vascular resistance (SVR), vascular resistance (VR), and mean heart rate (mHR).  **1.6 Echocardiography**  The echocardiogram parameters will encompass E/e’ ratio, left ventricular ejection fraction (LVEF), and wall thickening fraction (WTF). WTF is defined as [(end-diastolic wall thickness − end-systolic wall thickness)/ end-diastolic wall thickness] × 100 (%).  **1.7 Ultrasound examination of carotid plaques**  Ultrasonography of carotid plaques includes their location, size (length x width), and morphology as well as the intima-media thickness (IMT) and Crouse’s score of the common carotid artery.  **1.8 Six-minute walk test**  The six-minute walk test (6MWT) quantifies the maximal distance an individual can walk in 6 minutes, serving as an indicator of the patient's exercise capacity and cardiorespiratory fitness during routine physical activities.  **1.9 Short-term heart rate variability**  HRV refers to the fluctuation in the timing of consecutive heartbeats or the variance in heart rate. It is determined by the duration between two successive R-R intervals, representing the slight deviation between each cardiac cycle. HRV assessment will be conducted using the amor HRV Guard Analyzer (ZSY-1, Taiwan, China). With the patient at rest and in a supine position, short-term (5-minute) HRV will be measured during daytime hours.  **2.0 Tools for mental health assessment**  The Patient Health Questionnaire-9 (PHQ-9) is a critical instrument for the screening, diagnosis, and assessment of depression, enabling the measurement of its severity. Concurrently, the 7-item Generalized Anxiety Disorder Scale (GAD-7) enables the evaluation of generalized anxiety disorder. Similarly, the Pittsburgh Sleep Quality Index (PSQI) stands as a widely recognized assessment tool for determining sleep quality, and the Seattle Angina Questionnaire (SAQ) functions as a self-administered assessment tool designed to evaluate specific functional status and quality of life among individuals with CAD. |
| **Follow-up plan** | The patient was followed up at the end of the 1st and 3rd months post intervention. |
| **Sample collection** | √ Yes □No  10 ml/person of venous blood should be collected each time, for a total of 50ml/person for 5 sessions. |
| **Non-routine inspection** | □Yes √ No |
| **Statistical methods** | The baseline characteristics of both groups will be summarized using appropriate descriptive statistics. Analysis of both primary and secondary outcomes will be based on the intention-to-treat approach, ensuring that all participants remain assigned to their original group throughout the study.  Normally distributed data will be presented as the mean (standard deviation), and non–normally distributed data will be depicted as the median (interquartile range). Group comparisons will be conducted using independent sample tests, and within-group comparisons before and after treatment will be evaluated using paired sample tests. Clinical symptom variables will be portrayed as percentages. Categorical data will be assessed using either the chi-squared test or Fisher’s exact test. A significance level of.05 will be employed to interpret the P values. The statistical analysis will be conducted utilizing SPSS version 26 statistical software (IBM, Armonk, NY). |
| **Research risk self-assessment** | □ High-risk research □ Medium risk research √ Low-risk research  The group conducted relevant clinical studies at an early stage with positive results and no adverse effects. Previous studies have demonstrated the safety of cardiovascular ultrasound treatment modalities. The clinical trial is a multi-center clinical study with a large sample size, standardized design, high feasibility and low risk. |
| **Research Funding** | □ Fully funded by:  √ Partially funded by: Shenzhen Shengxiang High-tech Co., Ltd.  □ Nofunding  The research group signs horizontal project contracts with cooperative enterprises, and provides financial support on a regular basis according to the contracts. |
| **Corporate involvement** | □ No √ Yes  Company name: Shenzhen Shengxiang High Technology Co., Ltd  Company contact person: [name].  Enterprise contact to undertake the content: Technical information related to extracorporeal ultrasound therapy; 1 set of extracorporeal ultrasound therapy equipment; All consumables for extracorporeal ultrasound therapy required for the test. |
| **Other notes** | NO |

**Detailed study of the reference frame of the program**

**1 Introduction**

Coronary artery disease (CAD) is caused by atherosclerotic lesions in the coronary arteries, resulting in narrowing or blockage of the lumens of the vessels; this, in turn, causes myocardial ischemia, hypoxia, and necrosis ^[1]^. CAD has a high rate of morbidity and mortality and poses a severe threat to human health ^[2]^. Percutaneous coronary intervention (PCI) uses cardiac catheterization to improve myocardial perfusion by unblocking narrowed or occluded coronary arteries ^[3]^. As the least invasive revascularization procedure available, PCI has become the mainstay of treatment for CAD ^[4]^. However, as an invasive test and treatment method, it is often accompanied by a variety of postprocedural complications, including in-stent thrombosis or restenosis, no or slow reflow, arrhythmia, and an inflammatory response, which can significantly affect a patient’s condition and prognosis ^[5]^. Treatments for common complications after PCI include pharmacologic therapy, interventional repeat angioplasty, or stent implantation ^[5]^. However, medication can also lead to adverse effects, and such interventions as well as surgery are risky and costly ^[6]^. Therefore, there is new interest in the exploration of noninvasive, low-side-effect treatments to prevent postoperative complications and promote cardiac rehabilitation after PCI.

Cardiovascular ultrasound therapy cardiovascular ultrasound therapy, an emerging therapeutic tool, has attracted a great deal of attention because it has many biological effects and is noninvasive ^[7]^. Cardiovascular ultrasound therapy sends a mechanical force to the tissues; it has mechanical, cavitation, and low thermal effects, triggering reactions at the cellular and molecular levels ^[8]^. Previous studies have shown that cardiovascular ultrasound therapy promotes the expression of vascular growth factors, inhibits inflammatory responses and oxidative stress, reduces the apoptosis of cardiac cardiomyocytes, improves the microcirculation in ischemic tissues (thereby attenuating ischemia-reperfusion injury), and helps to protect cardiac function ^[7,9-13]^. In addition, cardiovascular ultrasound therapy has a good safety and tolerability profile ^[14,15]^. However, there are no relevant clinical research data to confirm the validity of these therapeutic effects; therefore, further studies are needed to determine the future role of cardiovascular ultrasound therapy in clinical use.

In order to clarify these issues, we designed a cardiovascular ultrasound treatment regimen for patients who had undergone PCI for CAD. In other words, we planned to conduct a multicenter, parallel-group, randomized controlled clinical trial to evaluate the rehabilitative efficacy of cardiovascular ultrasound therapy.

**2 Aims of the study**

Our study is intended to evaluate the rehabilitative efficacy of cardiovascular ultrasound therapy in patients with coronary artery disease (CAD) who had already undergone percutaneous coronary intervention (PCI). Specifically, the study aims to examine the effects of cardiovascular ultrasound therapy on inflammatory markers, serum lipids, endothelial function, cardiac function, carotid artery plaque, and hemodynamics. In addition, the study will analyze patients’ heart rate variability (HRV), record their symptoms, and score depression and anxiety.

**3 Study program**

**3.1 Study design and ethical approval**

This nonblinded, multicenter, parallel-group, randomized (1:1) controlled study will be conducted in 10 large hospitals in China, including Qilu Hospital of Shandong University, Qingdao Municipal Hospital, Yantai Yuhuanding Hospital, Linyi People’s Hospital, Tengzhou Central People’s Hospital, Weifang People’s Hospital, Jining No.1 People’s Hospital, Weihai Central Hospital, Liaocheng People’s Hospital, Dongying People’s Hospital, and Qilu Hospital of Shandong University (Qingdao). These hospitals were selected because of their significant experience and ability to recruit for PCI in cardiology as well as their ability to collaborate across disciplines to ensure that patients receive comprehensive treatment and rehabilitative support. The study protocol was reviewed and approved by the Ethics Committee of Qilu Hospital of Shandong University and other participating institutions (Ethics Committee reference number KYLL-202308-006). The study was registered on ClinicalTrials.gov, ID: NCT06640400.

Participants in this study will be recruited from the aforementioned medical institutions. Inclusion criteria call for hospitalized patients diagnosed (through laboratory and imaging tests) with CAD requiring PCI ^[16]^. Following consent from the patients or their family members, screening procedures will be conducted by medical professionals to ensure compliance with the eligibility criteria. Only those individuals meeting all recruitment criteria and no exclusion criteria will be included in the study.

**3.2 Participants: Inclusion and exclusion criteria**

**3.2.1 Inclusion Criteria:**

• Age at enrollment: 18 years or older;

• Confirmed CAD requiring elective PCI;

• Thrombolysis in myocardial infarction (TIMI) flow grade 2 or above after PCI;

• No intraoperative complications following PCI, such as entrapment, reflux, or perforation of the coronary artery;

• Intact skin in the anterior chest area;

• Cardiac enzymes and troponin I within normal range;

**3.2.2 Exclusion Criteria:**

• ST-segment elevation myocardial infarction and non–ST-segment elevation myocardial infarction;

• Occlusion of branch vessels during PCI;

• Perioperative use of hormones or immunosuppressants;

• Combined infection or other inflammatory diseases;

• Postoperative fever;

• Allergy to contrast media or cardiovascular ultrasound acoustic head–related materials;

• Changes in lipid-lowering, antiplatelet, and antihypertensive drug regimens during treatment;

• A clear diagnosis of autoimmune disease;

• A history of other surgeries or trauma in the preceding 7 days;

• Infection with the novel coronavirus during the preceding month;

• Previous PCI treatment;

• Previous cardiovascular ultrasound treatment;

• Diabetes mellitus.

**3.3 Criteria for the withdrawal of subjects from the trial**

**3.3.1 Subjects withdraw from the test on their own**

Patients can voluntarily withdraw from the trial at any time without providing any reason; or the subject has not explicitly withdrawn from the trial, but is no longer receiving LIPUS treatment or related indicators, it is also considered "withdrawal". Whenever possible, understand the reasons for the subject's withdrawal and document them in the case report form. Every effort should be made to keep the patient in the study and to continue with the required study-related treatments and markers.

For patients who voluntarily withdraw from the trial, the reason for withdrawal, the course of treatment, the time of the last treatment, and the results of the most recent test should be clearly recorded; The relationship between the branch or shedding in the trial and the trial should be carefully recorded, the possible impact of the discontinued case on the research conclusion should be analyzed, and the case report form should be completed and completed; Keep the original data of all exfoliated cases.

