**3.3.2 Withdrawal/drop-off as determined by the investigator**

The withdrawal decided by the investigator refers to the fact that the enrolled subjects are not suitable to continue the trial during the trial, and the investigator decides to withdraw from the trial.

1) During the trial, there are changes in the subject's condition, such as acute stent thrombosis, malignant arrhythmia, contrast nephropathy, acute left heart failure, hemodynamic instability, etc., which affect the compliance of continuing to participate in the trial or continue to participate in the trial may affect the safety of the subject, and the investigator believes that the patient should withdraw;

2) Patients with a definite diagnosis of PCI-related myocardial infarction at 48h;

3) Subjects who violate the inclusion/exclusion criteria, or have poor protocol compliance.

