**3.4 Calculation of sample size**

Our calculations of sample size and power are based on the primary outcomes, utilizing a two-sided analysis with a statistical power of 90 % (1 – β = 0.90) and a significance level of α = 0.05. Owing to the lack of prior studies examining cardiovascular ultrasound therapy following PCI, the sample size was determined following an extensive evaluation by a panel of experts. Targeting long-term inflammation and cardiovascular efficacy, they selected high-sensitivity C-reactive protein (hsCRP) as the primary biomarker, given its relevance and the larger sample size required by interleukin 6.

Cardiovascular ultrasound is estimated to reduce hsCRP levels by an average of 4 mg/L. To meet this target, 160 participants (80 per group in a 1:1 allocation) are projected to be needed. Factoring in an anticipated dropout rate of 20 %, the final sample size would be adjusted to 200 participants (100 per group), ensuring adequate statistical power and robustness for the study’s objectives.

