**3.7.2 Intervention description**

Participants allocated to the intervention group will undergo a 10-day regimen utilizing a medical cardiovascular ultrasound therapy device (838C-M-L-I/II, Shenzhen, China). The ultrasound instrument is equipped with a sound head comprising five transducer units operating at an ultrasonic frequency of 0.84 MHz with a sound intensity range of 1 W/cm^2^–1.25 W/cm^2^. The therapeutic ultrasound sessions require a controlled environmental temperature. Patients will assume the supine position, exposing the precordial region, with the 5-pronged head positioned parallel to the heart’s long axis; it should cover the entire precordial region including the right and left coronary arterial trunks and the aortic root (Fig.1). The five transducer units function sequentially in a scanning pattern, with each unit operating for 5 seconds and transitioning with a 0.5-second interval, following a clockwise rotation until the treatment has been completed. The cardiovascular ultrasound therapy device operates in a pulsed mode, and each treatment session lasts for 20 minutes; there would be two daily sessions for a total of 20 treatments. The control group was not given extracorporeal cardiac ultrasound therapy. Participants in the control group will not receive cardiovascular ultrasound therapy. cardiovascular ultrasound therapy will be assessed at baseline (24th-hour post-PCI), on the 10th day, and at the end of the first and third months post-intervention. If it is necessary to change the medication regimen as much as possible, if it is necessary to change the medication regimen, it should be decided after evaluation by the investigator, and if the medication regimen that does need to be changed has an impact on the test results, the patient should be excluded and the reasons for changing the medication regimen should be recorded in detail.

[figure not shown]

Fig. 1. Diagram of ultrasound head placement.

A: Patients undergoing cardiovascular ultrasound therapy. B is used in patients with occlusion of one coronary artery and C is used in patients with occlusion of both coronary arteries.

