**3.9 Outcomes**

**3.9.1 Primary outcome**

The primary outcome measures will focus on the levels of hsCRP and interleukin-6 in the peripheral serum following 20 cardiovascular ultrasound therapy sessions (i.e., on the 10th day). Comparative analyses will be conducted between the cardiovascular ultrasound therapy intervention and control groups along with pre- and postintervention assessments.

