**4** **Statistical analysis**

The baseline characteristics of both groups will be summarized using appropriate descriptive statistics. Analysis of both primary and secondary outcomes will be based on the intention-to-treat approach, ensuring that all participants remain assigned to their original group throughout the study.

Normally distributed data will be presented as the mean (standard deviation), and non–normally distributed data will be depicted as the median (interquartile range). Group comparisons will be conducted using independent sample tests, and within-group comparisons before and after treatment will be evaluated using paired sample tests. Clinical symptom variables will be portrayed as percentages. Categorical data will be assessed using either the chi-squared test or Fisher’s exact test. A significance level of.05 will be employed to interpret the P values. The statistical analysis will be conducted utilizing SPSS version 26 statistical software (IBM, Armonk, NY).

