**4.3 Analytic methods for handling protocol nonadherence and statistical methods for handling missing data**

We anticipate minimal missing data (<10%) for the primary outcome given that all participants will be in patients with regular daily contact maintained during treatment. The evaluation of missing data effects will involve comparing differences under plausible and extreme missing data scenarios. In the event of a significant primary test result, we will also assess the interaction size between group assignment and missing data necessary to render the difference nonsignificant. Should 10% or more of the baseline samples be excluded due to missing data, we will apply multiple imputation techniques for comprehensive analysis.

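### Stopping ultrasound can be read as withdrawal from the trial, a trigger only the ultrasound arm can meet, and beyond a general effort clause nothing requires the day-10 primary sample from these patients

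*Protocol*

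**What the plan says.** **Withdrawal.** Protocol section 3.3.1 covers patients who leave without saying so: where "the subject has not explicitly withdrawn from the trial, but is no longer receiving LIPUS treatment or related indicators, it is also considered" a withdrawal. The next request but one is "Every effort should be made to keep the patient in the study and to continue with the required study-related treatments and markers". For voluntary withdrawals the section then asks for the reason, the time of the last treatment and the latest available test result, and for an analysis of how discontinued cases might affect the conclusion. It does not mention further sampling.

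**Investigator withdrawal.** Section 3.3.2 lists clinical complications (item 1), PCI-related infarction at 48 hours (item 2) and, as item 3, "Subjects who violate the inclusion/exclusion criteria, or have poor protocol compliance".

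**Arms.** Section 3.7.2: "Participants in the control group will not receive cardiovascular ultrasound therapy". There is no sham. The ultrasound arm has two sessions a day for 10 days.

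**Primary outcome.** Section 3.9.1 places hsCRP and interleukin-6 "following 20 cardiovascular ultrasound therapy sessions (i.e., on the 10th day"). Section 3.9.2(3) also schedules inflammatory factors on day 10, with no condition on sessions received.

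**Analysis.** Section 4 plans intention-to-treat, "ensuring that all participants remain assigned to their original group throughout the study". Section 4.3 expects under 10% missing primary data. It plans plausible and extreme scenarios and, after a significant result, will "assess the interaction size between group assignment and missing data necessary to render the difference nonsignificant". Multiple imputation applies at 10% or more missing.

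**Adverse reactions.** Section 6.3, item 4, requires follow-up of patients who withdraw because of an adverse reaction, without naming a blood sample.

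**The concern.** Intention-to-treat needs the outcome from everyone randomised, including those who stop treatment. That works only if stopping treatment and leaving the study are kept apart. Section 3.3.1 can be read to merge them, and item 3 of section 3.3.2 does so for poor compliance.

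The merger is not even-handed. Only one arm has ultrasound to stop, and only that arm has 20 sessions to comply with. Section 3.9.1 also describes the primary sample by reference to 20 completed sessions, so a site could conclude that a patient who stopped part-way has no primary sample due.

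If such patients go unsampled and their day-10 inflammation differs from that of patients who continue, the ultrasound mean shifts without any treatment effect. Treatment is open-label, so the decision to stop may be related to how the patient is doing. Keeping a patient in the assigned group does not supply a value that was never measured. What blood is drawn after treatment stops is a matter of data collection, which a statistical analysis plan cannot repair afterwards.

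**Working it through.** **1. Which routes out of the trial apply to which arm**

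| Route | Ultrasound | Control |
|---|---|---|
| Explicit withdrawal (3.3.1) | yes | yes |
| No longer receiving ultrasound (3.3.1) | yes | cannot occur |
| No longer having related indicators (3.3.1) | yes | yes |
| Complications, infarction at 48 hours (3.3.2, items 1 and 2) | yes | yes |
| Eligibility violation or poor compliance (3.3.2, item 3) | yes | yes by wording, but no sessions to miss |

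One route is strictly one-sided, and item 3 falls mainly on the ultrasound arm.

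**2. The plan's own figures**

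From section 3.4: 4 mg/L reduction in hsCRP, two-sided alpha 0.05, power 90%, 80 per group, 20% dropout.

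- Dropout inflation: 160 / (1 − 0.20) = 200. This reproduces.
- No SD is given, so the 80 per group cannot be reproduced directly. Solving for the SD by normal approximation: SD = 4 / [(1.960 + 1.282) × √(2/80)] = 7.80 mg/L. With the t-test it is 7.76 mg/L, used below.

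**3. Bias if patients who stop are not sampled**

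Assumptions, none of them from the protocol: no true effect; a share p of the ultrasound arm stops and none of them is sampled; their mean day-10 hsCRP exceeds that of the remaining ultrasound patients by D; controls are fully observed; observed values only are compared.

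- Bias = p × D
- SE = √[SD²/100 + (SD² − p(1−p)D²) / (100(1−p))]
- Type I error = Φ(−1.96 + bias/SE) + Φ(−1.96 − bias/SE)

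Middle case, p = 10% and D = 0.5 SD = 3.88 mg/L: bias = 0.10 × 3.88 = 0.39 mg/L. SE = √(60.17/100 + 58.81/90) = 1.12. Bias/SE = 0.346. Type I error = 6.4%.

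| p | D | Bias, mg/L | Type I error |
|---|---|---|---|
| any | 0 | 0 | 5.0% |
| 5% | 0.25 SD | 0.10 | 5.1% |
| 5% | 0.5 SD | 0.19 | 5.3% |
| 10% | 0.25 SD | 0.19 | 5.3% |
| 10% | 0.5 SD | 0.39 | 6.4% |
| 15% | 0.5 SD | 0.58 | 8.1% |

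A simulation of 200,000 trials gave 0.39 mg/L and 6.3% for the middle case, and 0.58 mg/L and 7.9% for the last row. If D is negative, the bias has the same size but runs against ultrasound.

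**4. Set against the plan**

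- The largest bias shown is 0.58 / 4 = 15% of the target difference.
- Losing 15 of 100 ultrasound patients is 15 / 200 = 7.5% missing overall, below the 10% imputation trigger. The scenario and tipping-point analyses in section 4.3 would still run, the latter after a significant result.
- Power for 4 mg/L with 90 against 100 patients is about 94%, so lost power is not the issue.

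**The case against.** **The clause may mean something narrower.** No longer receiving A or B often means neither A nor B. On that reading, a patient who stops ultrasound but is still sampled is not a withdrawal, and the clause describes silent loss to follow-up. The English is awkward enough for either reading. This stands: the broader reading is possible, not established. It does not touch item 3 of section 3.3.2, which withdraws patients for poor compliance on any reading.

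**The protocol favours retention.** Section 3.3.1 urges continued treatments and markers, and hsCRP and interleukin-6 are the primary markers. Section 6.3 follows up adverse-reaction withdrawals. Patients are expected to be inpatients with daily contact. This lowers the risk. But an effort clause is not a requirement to sample someone already labelled withdrawn, and section 6.3 names no blood sample. Section 3.4 itself allows for 20% dropout.

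**Sensitivity analyses are planned.** They are, and they would show how fragile a result is. They do not recover values that could have been measured.

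**Stronger readings.** A reader might infer that the protocol orders sampling to stop once ultrasound stops; no sentence says so. A reader might infer that withdrawal as a whole is one-sided; most routes are open to both arms. A reader might infer that the bias must favour ultrasound; patients who stop because they feel well could have lower hsCRP, and nothing in the protocol settles the sign.

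**Conclusion.** The point holds as a badly fixed rule with probably modest consequences. Section 3.3.1 can be read to treat stopping ultrasound as leaving the trial, section 3.3.2 does so for poor compliance, and the treatment-stopping trigger exists in one arm only. The day-10 primary sample from these patients is encouraged in general terms but not required. This weakens the intention-to-treat analysis. To say that it invalidates the analysis would go too far, because group assignment is preserved and section 4.3 addresses missing values.

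The size and direction of any bias are unknown. Under the middle-case assumptions it is about 0.4 mg/L on hsCRP with a type I error of about 6.4%. With no difference between patients who stop and those who continue, there is none. These figures rest on an assumed one-sided loss, an assumed difference and a back-solved SD. Interleukin-6 was not quantified, since the protocol gives no planning values for it. The change is worth making because it is cheap and can only be made before the samples are missed.

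**What to change.** - **Sections 3.3.1 and 3.3.2:** separate stopping ultrasound, or poor compliance, from withdrawal from the study. Let only withdrawn consent or loss to follow-up end data collection. Keep the existing retention sentence and add: *Patients who stop ultrasound for any reason keep the day-10, month-1 and month-3 assessments.*
- **Section 3.9.1:** state that the day-10 sample is drawn in every randomised, consenting patient, whatever number of sessions was received. Record sessions received as adherence data.
- **Section 4.3:** keep the planned analyses for values that are still missing.

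**Cost.** Wording in three sections. If 10 of 100 ultrasound patients stopped, at most 10 × 3 = 30 already scheduled assessments would be kept that might otherwise be lost. At 10 mL per draw that is 30 mL per patient, within the 50 mL planned under Sample collection in the protocol summary. Patients discharged early may occasionally need a day-10 return visit. Sample size and treatment do not change.
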